### Safety and tolerability

Despite the good safety profile of LSD [40], surveys of psychedelic microdosers often report mild side effects. These include psychological effects, such as racing thoughts or increased anxiety, and physiological effects, such as headaches or sleep problems [41]. However, not everyone who microdoses report side effects. Among an online sample of psychedelic microdosers, 30% reported no side effects [41], and in another online study of 1116 microdosers, only 20% of the sample reported adverse effects [42]. Furthermore, these effects are reported to be acute rather than persisting long term. However, results from observational research need to be verified in more scientifically rigorous trials, as variability in microdosing practices, dosages, quality of substances, and measurement time points limit the validity of the results.

To date, several laboratory-based randomised controlled trials have explored the effects and safety of LSD microdosing. Excluding the MDLSD study [39] (see below), five studies with unique samples have been conducted. Safety data collected in these trials consisted primarily of blood pressure, heart rate, and basal body temperature. The first tested three doses of LSD tartrate (6.5, 13, 26 μg) compared to placebo in a within-subjects design [43]. Participants in this study reported dose-dependent increases on the 5D-ASC, a scale used to measure consciousness-altering effects. An increase in blood pressure, but not body temperature or heart rate, was observed at the 13 and 26 μg doses, an effect observed in other research [38, 44]. No other safety data or adverse events were reported. In another study, the highest dose produced modest subjective effects, including increased ratings of ‘feeling a drug effect’, significant peak change scores on the Profile of Mood States Vigor subscale, and ratings of stimulant-like and LSD-like effects [45]. However, no effects on any cardiovascular measures were reported.

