**Fig. 1 Fig1:**
[figure not shown]
Schedule of enrolment, interventions, and assessments (abbreviated) NB: HD = Home dosing, *Medical History, Height, Weight, and Blood test, † AKPS, Change in Medication, Health Status Review, ‡ LAP-R-PMI, FACIT-SP-12, Demoralisation Scale, SAHD, and WCS

Participants will be referred by regional cancer services or contact the study team directly in response to study advertisements.

Participants will all have a diagnosis of stage IV solid tumour cancer and moderate to severe distress, as identified by our screening questionnaire [55]. Half of the sample will identify as Māori, and the other half will identify as non-Māori. Participants will be required to meet the full inclusion and exclusion criteria outlined in Tables 1 and 2. Initial screening phone calls will be conducted with participants to explain study participation and inclusion/exclusion criteria and to establish the current level of distress on a scale from 1 to 10 (distress thermometer [55]).

**Table 1 Tab1:** Full inclusion criteria

	Inclusion criteria
Consent	Willing and able to give informed consent for participation in the trial, reconfirmed verbally at each clinic visit
	Agree to have study visits video and/or audio recorded
	Agree to inform the Investigators within 48 h of any medical conditions and procedures being undertaken
	Willing for the investigators to communicate directly with their medical team to determine medical suitability for study participation (oncologist, GP, palliative care physician, etc.)
	Agree to refrain from starting any new psychiatric medication and/or psychotherapy during the study period
	Agree to have transportation other than driving themselves to where they are staying on the days of medication dosing
	Able and willing to be contacted via telephone for all necessary telephone contacts
	Agree to use an effective form of contraception if of child-bearing potential for the duration of medication dosing
	Must provide a contact/support person if they are unreachable by study staff or in the event of severe distress or suicidality
	Agree to not use any medications on the prohibited medications list during the study
	Agree not to take any herbal supplement for the duration of medication dosing (except with prior approval of the research team)
Demographics	At least 25 years old
	Proficient in speaking and reading English
Clinical characteristics	Diagnosis with an incurable stage IV incurable solid organ malignancy

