	Prognosis of at least 6 months life expectancy from the time of screening
	Moderate distress (4 or greater) as measured by the distress thermometer

**Table 2 Tab2:** Full exclusion criteria

	Exclusion criteria
Treatment	Currently participating in a clinical trial of a systemic anti-cancer treatment
Physical health	Pregnant or lactating BMI < 18.5
	Diagnosis of cerebral metastases
	Karnofsky performance scores below 50 or other physical limitations that preclude participation in weekly psychotherapy and microdosing of LSD
Lab work	Liver function test > 3 times the upper limit of normal or creatinine clearance < 30 mL/min
Diagnosis	Have a current diagnosis or history of any medical condition that could make receiving a sympathomimetic drug harmful because of potential increases in blood pressure and heart rate as assessed by a study physician
Vital signs	Cardiovascular conditions including abnormal heart rate seen by ECG
	Blood pressure not exceeding 160 mmHg (systolic) and 90 mmHg (diastolic) (measured at three time points)
Mental health	
Diagnosis	Lifetime history of schizophrenia or other psychotic disorders, or bipolar I or II disorder as assessed by the Standard MINI (Standard version 7.0.2)
	A current diagnosis of PTSD, panic disorder, agoraphobia, OCD, anorexia, and bulimia as assessed by the Standard MINI (Standard version 7.0.2)
Current risk	Elevated risk of suicide as determined by the Columbia-Suicide Severity Rating Scale (C-SSRS) or by a study psychiatrist
Drug use	Any lifetime history of psychedelic microdosing; defined as repeated low-dose psychedelic usage for more than a week at a time
	Use of a psychedelic within the last year
	Recent or current use of illicit drugs including methamphetamine, heroin, and synthetic cannabis. Other non-prescribed drugs will prompt exclusion at the discretion of a study physician
	Current THC/cannabis usage will prompt exclusion if the participant does not agree to cease. However, CBD is permitted, and usage will be recorded

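### The blood-pressure row of the exclusion table states the acceptable range, so read literally it excludes patients within 160/90 mmHg and does not exclude those above it

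*Protocol article*

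**What the plan says.** Table 2 of the protocol article is headed "Full exclusion criteria". Under vital signs it lists "Blood pressure not exceeding 160 mmHg (systolic) and 90 mmHg (diastolic) (measured at three time points".

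The Study design section makes the tables binding: "Participants will be required to meet the full inclusion and exclusion criteria outlined in Tables 1 and 2". Table 1, the inclusion criteria, has no blood-pressure entry, and no other part of the article gives a blood-pressure limit for eligibility.

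Other numeric rows of Table 2 describe the patient who is to be kept out, for example "Liver function test > 3 times the upper limit of normal or creatinine clearance < 30 mL/min" and "Karnofsky performance scores below 50 or other physical limitations that preclude participation". The table also excludes conditions that "could make receiving a sympathomimetic drug harmful because of potential increases in blood pressure and heart rate as assessed by a study physician".

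**The concern.** The row describes an acceptable blood pressure but stands in a list of reasons for exclusion. Its wording and its heading point in opposite directions, and no other statement in the article settles which one governs.

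The row is a safety threshold. The Safety and tolerability section says of one earlier low-dose LSD study: "An increase in blood pressure, but not body temperature or heart rate, was observed at the 13 and 26" μg doses, and adds that other research saw the same effect. The Titration protocol section allows doses up to 20 μg, so 13 μg is within this trial's range. The evidence is mixed: the same section describes a study with no cardiovascular effect, and the earlier healthy-volunteer microdosing trial found no change in vital signs. Even so, the sympathomimetic row shows that the authors regard a rise in pressure as a possible harm. Six of the 13 doses (days 4, 11, 18, 25, 32 and 39) are taken at home, so the pressure at which a patient may enter matters. Safety is also one of the primary objectives.

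**Working it through.** The plan has no figure to reproduce here. The check is one of logic.

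**Inputs.** S is systolic and D is diastolic pressure in mmHg. The limits 160 and 90 come from Table 2. The four test pressures are illustrations chosen for this check and are not trial data.

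**Step 1: the row as printed.** An exclusion criterion removes a patient when its statement is true. The printed statement is true when S ≤ 160 and D ≤ 90, so the literal rule is: exclude if S ≤ 160 and D ≤ 90.

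**Step 2: the evident intent.** To be acceptable, a patient must be within both limits. The patients to exclude are all the others, and the negation of (S ≤ 160 and D ≤ 90) is (S > 160 or D > 90).

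**Step 3: the shortest edit.** Deleting *not* and keeping *and* gives: exclude if S > 160 and D > 90. This is not the negation, because it catches only patients above both limits.

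**Step 4: the three rules applied.**

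| Pressure | As printed | *not* deleted, *and* kept | Exceeding 160 or 90 |
|---|---|---|---|
| 120/75 | excluded | not excluded | not excluded |
| 165/85 | not excluded | not excluded | excluded |
| 150/95 | not excluded | not excluded | excluded |
| 180/100 | not excluded | excluded | excluded |

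The printed rule is wrong for all four patients. The shortest edit corrects 120/75 and 180/100 but remains wrong for 165/85 and 150/95, each of whom is above one limit only. The rule with *or* is right for all four.

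**Step 5: whether this is the table's style.** BMI below 18.5, Karnofsky below 50, liver function above 3 times the upper limit of normal and creatinine clearance below 30 mL/min all name the disqualifying value. The blood-pressure row is the only numeric row that runs the other way. The sentence is complete and sits under the right heading, so nothing suggests a fault in the text extraction.

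**The case against.** The strongest reply is that nobody would follow the row literally. Doing so would turn away every patient with normal pressure, which is absurd and contradicts the sympathomimetic row of the same table. On that view this is an editorial slip that alters no limit, endpoint, estimate or sample size.

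Other safeguards also remain. A patient at 180/100 still faces the physician's judgement on sympathomimetic risk and the row on cardiovascular conditions. Eligibility is checked at screening and reconfirmed at each site visit, and vital signs are taken before the first dose. Finally, the Trial status section says that the full protocol is at version 1.6 and that recruitment has begun. That document is not shown, so the error may exist only in the article.

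Much of this stands. The intended direction is clear, a single centre would probably apply it, and whether the screening form carries the same wording is unknown. It is also right that an exclusion row admits nobody; the exact statement is that this row does not itself exclude patients above the limits.

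The reply does not make the row correct. The other safeguards rest on judgement and supply no numeric cut-off. A reader who reverses the row mentally can still go wrong on the patient above one limit only. This is also not a detail that an article leaves to the full protocol: it is a rule that the article states, and states the wrong way round.

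**Conclusion.** The concern holds. As published, the blood-pressure exclusion is inverted: it excludes patients at or below both 160 mmHg systolic and 90 mmHg diastolic, and does not exclude those above either limit.

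The practical effect is likely small, on the assumption that site staff apply the evident intent and that the physician assessment and pre-dose checks work as described. No analysis or sample size figure depends on it. It should still be corrected. It is the only numeric blood-pressure limit for entry, and the Discussion presents this trial as the foundation of a larger one, in which the criteria may be reused.

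**What to change.** Replace the row in Table 2 with: *Blood pressure exceeding 160 mmHg systolic or 90 mmHg diastolic (measured at three time points)*. Both changes are needed: *not* comes out, and *and* becomes *or*. Alternatively, move the present wording unchanged to Table 1, where it would be correct as an inclusion criterion.

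The cost is one line in the eligibility table, plus the same line in the full protocol and the screening form if they repeat this wording. The limits do not change.

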### Outcomes

Primary and secondary outcome measures are outlined in Tables 4 and 5. Feasibility measures include adherence to medication regimen, attendance at MCP sessions, MCP treatment fidelity, and participant recruitment and attrition rates; the feasibility targets (detailed below) are based on previous research [21, 22]. Acceptability will be assessed using open-ended questions (T0–T9) and semi-structured qualitative interviews at baseline and at the one and 6-month follow-ups. Furthermore, the completeness of data will also be used to indicate the acceptability of completing study measures. Safety assessments include physiological data (HR, BP, body temperature), weekly symptom reporting, adverse event reporting, and ECG taken on the last study visit.

**Table 5 Tab5:** Secondary measures

Outcome domain	Measure	Scale
Sense of meaning	Personal Meaning Index of the Life Attitude Profile – Revised (LAP-R) [56]	16 items, 7-point Likert scale from 1 (strongly agree) to 7 (strongly disagree). Scores are summed
Quality of life	Functional Assessment of Chronic Illness Therapy – General (FACT-G) [57]	27 items, 5-point Likert scale from 0 (not at all) to 4 (extremely). Four subscales, summed
Spiritual well-being	Functional Assessment of Chronic Illness Therapy – Spiritual Well-being 12-item scale (FACIT-SP-12) [58]	12 items, 5-point Likert scale from 0 (not at all) to 4 (very much). Scores are summed
Sense of connectedness	Watts Connectedness Scale [59]	19 items, rated on VAS (0–100), anchors: ‘Not at all’ and ‘Entirely’. Three subscales, reported as mean scores and subscale means
Anxiety and depression	Depression, Anxiety and Stress Scale (DASS-21) [60]	21 items, 5-point Likert scale, from 0 (never) to 4 (almost always). Three subscales, reported as summed scores (each subscale sum multiplied by two)
	Hospital Anxiety and Depression Scale (HADS) [61]	14 items, 5-point Likert scale (0–4). Two subscales, reported as summed scores
Te Whare Tapa Wha Mental Health outcomes	Hua Oranga [62]	14 items, 5-point Likert Scale (1–5). Four subscales, reported as subscale or total questionnaire summed scores
Demoralisation	Demoralization Scale [63]	24 items, 5-point Likert scale, ranging from 0 (never) to 4 (all the time). Five subscales, reported as summed scores
Attitudes towards death	Schedule of Attitudes towards Hastened Death (SAHD) [64]	20 items, scored 0 (false) or 1 (true), reported as a total sum
Personality	Big Five Inventory (BFI-2-XS) [65]	15 items, 5-point Likert scale, ranging from 1 (disagree strongly) to 5 (agree strongly). Five subscales, reported as summed scores
Therapeutic alliance	Working Alliance Inventory Short Form (WAI-SF) [66]	12 items, 5-point Likert scale, ranging from 1 (seldom) to 5 (always). Three subscales, reported as summed scores
Altered states of consciousness	5-Dimensional Altered States of Consciousness Rating Scale (5D-ASC) [67]	94 items, with 5 scales and 11 subscales reported as % of the maximum score
Personality: absorption	Modified Tellegen Absorption Scale (MODTAS) [68]	34 items rated on a 5-point scale (0–4) reported as the sum of scores (0–136)
Treatment expectancy	Treatment Expectancy Questionnaire [69]	15 items rated on an 11-point Likert scale
Pain	Brief Pain Inventory – Short Form (BPI-SF) [70]	4 severity items and 7 interference items, rated on an 11-point Likert scale, ranging from 0 (no pain/does not interfere) to 10 (pain as bad as you can imagine/completely interferes), the two subscales are reported as means
Measurement of blinding	Dose Day Questionnaire	Single-item measure (placebo, LSD, don’t know)
Subjective drug effects	Drug Effects Visual Analogue Scale [39]	12 items, rated on VAS (0–100), reported individually and as mean score
Caregiver stress – support person only	Kingston Caregiver Stress Scale [71]	10 items, rated on 5-point Likert scale, reported as the sum of scores (10–50)
Closeness to others – support person only	Inclusion of Other in Self [72]	Single-item measure, between 1 and 7

The schedule of assessments is detailed in Fig. 1. Key time points for psychometrics are days 1, 22, and 43, as well as the 1- and 6-month follow-ups (see Fig. 1). In addition to psychometrics, vital signs and serotonin syndrome checks will be conducted at every in-clinic visit. Participants will also record adherence to dosing, subjective drug effects, measurement of blinding, and any adverse events on home dosing days.

### Participant recruitment

Adult Māori (*n* = 20) and non-Māori (*n* = 20) patients with a diagnosis of stage IV cancer and depression and/or anxiety will be referred by regional cancer services or patient self-referral. Participants must be willing for the Investigators to communicate directly with their medical team to determine suitability and whether they have adequate physical status for study participation. Recruitment is estimated at one participant per week for 40 weeks (10 months) based on the recruitment rate of cancer patients through a similar study [73]. Interested participants will contact researchers to express interest after seeing advertisements or will provide consent to be contacted by researchers following referral by health professionals.

### Randomisation, masking, and code-breaking

A biostatistician ([name]) will perform randomisation of the allocation of participants to the interventions. The biostatistician will generate a randomisation code list, and participants will be randomised in randomly permuted blocks with stratification used to give separate lists for Māori and non-Māori. The active and placebo interventions will be matched in appearance. Only the biostatistician and pharmacists involved in the study will be unblinded to study group allocation. These persons will not interact with study participants and will not be present during any drug administration sessions. To ensure allocation concealment when a participant enters the trial, they will then be allocated by a blinded investigator to the first available code on the randomisation sequence list. Both participants and Investigators will be kept blinded until the End of Trial. The Start of Trial is the date of the first screening visit for the first potential participant. The End of Trial is the date of the last 1-month follow-up interview of the last participant. Each participant is considered an active trial participant from the first screening visit until 1-month follow-up unless otherwise withdrawn. In case of emergency, study pharmacists will also keep an electronic spreadsheet of allocations so that de-blinding can be performed rapidly.

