Outcome domain	Measure	Definition
Feasibility	Adherence to medication regimen	Compliance with study treatment (at minimum 80% of doses taken indicates feasibility, i.e. 11 out of 13 doses taken)
	Attendance at MCP session	Percentage of participants attending 4 out of 7 sessions
	MCP treatment fidelity	Rating on the Memorial Sloan Kettering Fidelity Rating Scale. A 5-item yes/no indicating presence of content, a 5-item 3-point Likert scale measuring coverage, and a final 5-point Likert scale assessing overall focus on meaning/purpose
	Participant recruitment	Percentage of consented participants randomised (70% or greater indicates feasibility)
	Attrition	Number of dropouts following randomisation (30% or less indicates feasibility)
Acceptability	Qualitative interviews	Semi-structured qualitative interviews at baseline and at 1 month following treatment completion (T8) (participant and support person) and will address expectations and the acceptability of study procedures
	Completeness of data	Percentage of complete data
Safety	Vital signs	Monitoring of vital signs including heart rate, blood pressure, and body temp at 0, 30, 120, 240, and 360 min post-administration at T1. Also measured at 0- and 45-min post-administration, for T2–T7. Serotonin syndrome checks on every in-clinic day T1–T7
	Palliative Care Outcomes Collaborative Symptom Assessment Scale (PCOC-SAS)	Nine symptom items on an 11-point scale of distress, rated from ‘absent’ to ‘severe’
	Adverse events	Participants are asked on dosing days to report any ‘unpleasant health effects’ and to rate them as mild, moderate, or severe
	ECG data	ECG data will be reviewed by a study physician, noting where reference ranges are exceeded

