### Data collection and management

Case report forms (CRFs) will be entered into the online Research Electronic Data Capture (REDCap) tool hosted at the University of Auckland by study researchers for each participant. This will include demographics, medical history, height, weight, current medications, notes on physical examinations, vital signs, and adverse events at the study site. REDCap is a secure, web-based software platform that supports data capture for clinical trials.

ECG results will be electronically appended to the CRF. All subsequent psychometric measures will be completed by participants directly into REDCap, and qualitative interviews will also be captured electronically. Serum chemistry and haematology, biomarker, and pharmacokinetic data will be received electronically from subcontracted laboratories. Tissue samples will be used for analyses as described in the protocol for screening purposes only. No tissue samples will be kept for the purposes of the study or for further analysis.

All electronic data will be stored on secure University of Auckland servers, which include password protection, multi-site backups, and tape archiving. An original, unprocessed version of every data file will be kept on the servers such that these files may only be modified by a University of Auckland IT systems administrator, thus ensuring the fidelity and audit capability of all electronic data. Scanned versions of all paper-based CRFs and source data formats will be made and held on the servers in password-protected files to ensure the fidelity of these data and allow future audits of extracted data.

Participants will be identified by a unique trial-specific number and/or code in any electronic database. On all trial-specific documents, other than the signed consent form, prescriptions, and page one of the CRF (separately filed), the participant will be referred to by the trial participant code, not by name. All source data including that contained in the CRFs and the Trial Master File (TMF) will be held for a period of 15 years from the completion of the trial.

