This study’s aims are to assess the feasibility, acceptability, and safety of psychedelic microdosing-assisted meaning-centred psychotherapy. The delivery of microdoses alongside psychotherapy in cancer patients has not yet been researched; cancer patients are vulnerable with complex health and psychological needs, and these characteristics make conducting research and designing new interventions more challenging. This feasibility trial is critical in establishing an appropriate treatment regimen that is not unduly burdensome. These findings will form the foundation of a larger-scale RCT to test the efficacy of this potential treatment. There are several design factors to consider when working with an unwell population who may be receiving concurrent cancer treatment including the appropriate dosage and dosing schedule, the practicality of attending weekly MCP sessions, and the acceptability of MCP delivered over Zoom as an alternative to in-clinic sessions. This feasibility trial will also give an indication of recruitment patterns and levels of interest in the study population. Although previous research has indicated that there would likely be a high degree of uptake of psychedelic-assisted psychotherapy in this sample [76], this is the first study of its kind to offer this treatment. Furthermore, attrition rates will not only inform future RCT design but will provide valuable data on feasibility and acceptability. Finally, collecting rigorous safety data is essential for ongoing research and the potential future implementation of psychedelic-assisted therapy into general health practices.

At the feasibility stage of research, incorporating qualitative methodologies is important. In this current work, qualitative interviews conducted at baseline and at the 1- and 6-month follow-ups will provide rich data that will complement and expand on quantitative findings. Semi-structured interviews will ask participants about their expectations, knowledge of psychedelics, their experience of taking medication, attending MCP sessions, completing the study measures, and about any benefits or negative effects of the intervention. Family members are also included in the study design by asking them to complete brief psychometrics and qualitative interviews at baseline and 1-month follow-up. This data will add richness and build on data collected from participants which will benefit future work.

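### Blinding is guaranteed only to the last 1-month follow-up, so the code may be released before some 6-month self-report outcomes are collected

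*Protocol article*

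**What the plan says.** All three statements that fix the blind stand in the protocol article under 'Randomisation, masking, and code-breaking':

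- The duration of the blind: "Both participants and Investigators will be kept blinded until the End of Trial".
- The date at which it ends: "The End of Trial is the date of the last 1-month follow-up interview of the last participant".
- The participation window, which closes at the same visit: "Each participant is considered an active trial participant from the first screening visit until 1-month follow-up unless otherwise withdrawn".

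Outcome collection runs longer. Under 'Outcomes': "Key time points for psychometrics are days 1, 22, and 43, as well as the 1- and 6-month follow-ups". Under 'Data collection and management', these measures are self-reported: "All subsequent psychometric measures will be completed by participants directly into REDCap". The mixed models under 'Statistical analyses' include treatment, time over T0–T9 and their interaction. Table 4 labels the 1-month visit T8, so T9 is read here as the 6-month visit.

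On interviews the article disagrees with itself. 'Outcomes' plans "semi-structured qualitative interviews at baseline and at the one and 6-month follow-ups", and the Discussion repeats it: "qualitative interviews conducted at baseline and at the 1- and 6-month follow-ups will provide rich data". Table 4, which defines the acceptability measure, lists interviews only at baseline and T8.

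**The concern.** The promise of blinding runs out at T8 of the last participant, while data that feed a treatment comparison are still due at T9. If the code is released at that point, later entrants would answer the 6-month questionnaires knowing their allocation, and earlier entrants would have answered them blind. Both sets would enter one model.

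The article itself explains why this matters. Under 'Scientific basis for current study design' it reports that expectancy was associated with improved well-being, that unblinding may bias effect sizes, and that the earlier healthy-volunteer trial saw functional unblinding. It therefore tells participants that three placebos are in use when only the inactive one is. The 'Titration protocol' section adds wording to protect the blind further. Releasing the code before T9 would undo both safeguards for the 6-month data. Under 'Objectives', the secondary measures are meant to indicate clinically meaningful change and supply sample-size inputs for the larger trial, so a distorted 6-month contrast could carry into that design.

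**Working it through.** The article gives no figure for how many 6-month visits fall after End of Trial, so the count is built from its schedule.

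**Inputs**

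- N = 40, one entrant per week ('Participant recruitment'), so participant *i* enters at week *i* − 1 and the last at week 39.
- Treatment lasts 43 days = 6 weeks 1 day = 6.14 weeks. The article's maximum reproduces: 6 weeks 1 day + 7 break weeks = 13 weeks 1 day.
- T8 is 1 month after treatment completion (Table 4).
- T9 is 6 months. Its starting point is not stated; end of treatment is assumed first.
- One month = 365.25/12/7 = 4.35 weeks, so 6 months = 26.09 weeks.

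**Base case**

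1. End of Trial = 39 + 6.14 + 4.35 = week 49.5.
2. T9 of participant *i* = (*i* − 1) + 6.14 + 26.09 = (*i* − 1) + 32.23.
3. T9 is outstanding when (*i* − 1) + 32.23 > 49.49, that is *i* − 1 > 17.26, so *i* ≥ 19.
4. Entrants 19 to 40 qualify: 22 of 40 = 55%.

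Equivalently, with entries *s* weeks apart and a T8-to-T9 gap of *G* = 5 × 4.348 = 21.74 weeks, the count is floor(*G*/*s*) + 1.

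**Sensitivity, one change at a time**

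| Change | T9 outstanding, of 40 |
|---|---|
| None | 22 |
| T8 at 4 weeks, T9 at 24 or 26 weeks | 20 or 22 |
| Accrual over 52 weeks (*s* = 1.3; 21.74/1.3 = 16.7) | 17 |
| Accrual over 65 weeks (*s* = 1.625; 13.4) | 14 |
| Accrual over 80 weeks (*s* = 2; 10.9) | 11 |
| Only the last participant uses all 7 break weeks (21.74 − 7 = 14.74, so 14 others plus the last) | 15 |
| 6 months counted from day 1 (21.74 − 6.14 = 15.60) | 16 |
| 0–7 random break weeks each (simulated; End of Trial at the latest T8) | mean about 21; 95% of runs 17–25 |

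Combining 80-week accrual with a day-1 starting point gives floor(15.60/2) + 1 = 8. No scenario gives zero, because the last participant's T9 always follows that participant's own T8.

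**Attrition.** With the article's 30% feasibility limit falling evenly over entry order, 22 × 0.7 = 15.4 of 28 remain, still 55% of those followed.

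**Effect on the estimate.** If knowing allocation shifts the treatment difference by δ in those affected, and they are a fraction *f* of each arm at T9, the T9 contrast shifts by roughly *f*δ: 0.55δ at 22 of 40, 0.275δ at 11 of 40. The documents give no value for δ, so the bias itself cannot be sized.

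**After the fix.** The blind holds to week 39 + 6.14 + 26.09 = 71.2 instead of 49.5, a shift of 21.7 weeks or 5 months, and no T9 visit falls after code release.

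**The case against.** - **Permission is not instruction.** The blinding sentence sets a minimum. Nothing schedules code release, notification or debriefing on that date, and the full protocol (version 1.6), which is not shown, may set out those steps. This stands, and everything said about consequences is conditional on release. It does not remove the point: the article does not merely leave the end of the blind open, it fixes it at the wrong visit. The participation window closes at the same visit, so a slip of one word is unlikely.
- **Little of the primary evidence is exposed.** The objectives are feasibility, acceptability and safety, and the sample size section disclaims significance testing. Dosing, session attendance, vital signs and recruitment are finished by T8, and the questionnaires at days 1, 22 and 43 and at 1 month stay blinded for everyone. This largely stands and lowers the severity. Acceptability is only partly clear of it, since 'Outcomes' uses open-ended questions up to T9 and 6-month interviews.
- **The interview part is contested.** Table 4 stops interviews at T8. This stands; the finding rests on the questionnaires, and the interview schedule must be reconciled.
- **About half is near the top of the range.** This stands. Table 1 asks for a prognosis of only 6 months from screening, while T9 falls at least 32.2 weeks (7.4 months) after the first dose when counted from end of treatment. Fewer than 22 people would probably supply affected data.

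**Conclusion.** The contradiction holds: blinding is guaranteed to T8 of the last participant, while self-reported outcomes that enter the treatment-by-time model are collected to T9. On planned accrual, with T9 timed from end of treatment and no break weeks, 22 of 40 participants would have T9 outstanding. Slower accrual, a late finisher or a day-1 starting point, taken singly, give roughly 11 to 22, before attrition. Reading T9 as the 6-month visit is an inference from Table 4.

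A reader might infer that later entrants' 6-month data will be open-label, or that the trial's primary conclusions are compromised. The documents support neither. Release at End of Trial is allowed, not prescribed, and the exposure is mainly one late time point of secondary outcomes in a feasibility trial. It should be fixed, and before any code is released, because blinding cannot be restored afterwards.

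**What to change.** Tie code release and participant debriefing to the last participant's 6-month follow-up (T9) and database lock. There are two ways:

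1. Redefine End of Trial, with the active-participation window, as that date.
2. Leave End of Trial alone and state a separate code-break date. This is narrower, because extending active participation may also affect the adverse-event window, which is defined by the last study visit.

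If 1-month results are wanted earlier, only the statistician who is already unblinded should analyse them. Participants and all staff who collect follow-up data should stay blind, and participants not debriefed, until every participant's T9 is complete. The condition must refer to all participants: the first entrant reaches T9 at about week 32, while recruitment runs to week 39, so individual release could disclose the deception while others are still entering or under treatment. Emergency unblinding is unaffected.

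In the same amendment, reconcile Table 4 with 'Outcomes' and the Discussion on 6-month interviews, and state the starting point for the 6-month visit.

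Cost: a short amendment, code release and debriefing about 5 months later, and possibly an ethics notification because the deception is prolonged in patients with advanced cancer. No change to sample size, visits or measures is needed.
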